### Randomization

Participants will be recruited consecutively. All patients meeting the inclusion criteria and providing informed consent are randomly assigned to the IG or CG by a study nurse at the time of their PR approval. Randomization will be stratified according to age. The randomization list (with computer-generated random numbers) is created by the Department of Medical Psychology and Psychotherapy, Medical Sociology and Rehabilitation Sciences at the University of Würzburg (concealed allocation).

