**Methods:**

The EPRA study is a single-center randomized controlled waiting-list trial in the Bad Reichenhall Clinic. Inclusion criteria include a referral diagnosis for uncontrolled asthma, no cognitive impairment and no very severe co-morbidities that indicate significantly greater illness morbidity than asthma alone. In the intervention group (IG), participants will start PR within 4 weeks after randomization; participants of the control group (CG) will start PR 20 weeks after randomization. Data will be assessed at randomization (T0), after 4 weeks (T1; IG: begin of PR), 7 weeks (T2; IG: end of PR), and 20 weeks (T3, CG: begin of PR). The primary outcome is asthma control at T2/T3. Secondary outcomes are health-related quality of life, functional exercise capacity, dyspnea, anxiety, depression, subjective self-management skills, illness perceptions, sick leave and subjective work ability. Outcomes will be analyzed with analysis of covariance, including baseline values of the respective outcomes as covariates. Healthcare costs will be analyzed with a gamma model with a log-link.

A longitudinal follow-up study will generate additional data at 3/6/9/12 months after PR for both IG and CG. Latent change models will be used to analyze the course of the primary and secondary outcomes. Annual cost differences before and after rehabilitation will be compared by paired t-test.

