### Sample size

Calculation of sample size is based on our primary outcome, the ACT, assessed three months after the inpatient rehabilitation. A previous longitudinal study of asthma patients in the Bad Reichenhall Clinic (without a CG) showed changes between start of inpatient rehabilitation and three months after inpatient rehabilitation of (Cohen’s) d > 0.5 [25]. However, this value might overestimate the effect of inpatient rehabilitation compared to a control group. Therefore, sample size was calculated to detect a difference of d = 0.3 at T3 between the IG and CG. Using alpha = 0.05 and power = 0.8, 352 participants are required, but assuming a drop-out rate of 30%, a total of n = 504 patients will be recruited [26].

Latent curve models will be used to analyze the course of the primary outcome in the longitudinal follow-up study. As a rule of thumb, N > 100 cases should be included in the computation of these models. Even with a conservatively estimated drop-out rate of 50% until T6 for IG and T8 for CG, N = 152 patients would remain in the study, which is sufficient.

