### Statistical methods

Primary and secondary outcomes will be analyzed according to the intention to treat approach [56]. All randomized patients will be included in the analysis. Missing data fulfilling the assumption of missing (completely) at random will be imputed using multiple imputation procedures [57]. In addition, because it may be possible that some patients will not start with the inpatient rehabilitation or decide to drop-out of the study, we will also analyze results based on a “per protocol” approach [58, 59] including only patients remaining in the study until T3.

The analysis of the primary and secondary outcomes at T2/T3 will use analysis of covariance (ANCOVA) with treatment group as a fixed effect and baseline value of the respective outcome as a covariable. Adjusted mean differences and confidence intervals will be reported. In addition, moderating effects [60] of the following baseline variables on the primary outcome will be analyzed: ACT, gender, age, quality of life (assessed via SGRQ Total Score), anxiety (assessed using GAD-7) and depression (assessed using PHQ-7). For all models, statistical model assumptions (linearity, homoscedasticity, normality of residuals) will be tested. If model assumptions are violated, appropriate analysis methods (e.g. robust regression, log-transformation) will be used.

Latent change models will be used for exploratory analyses of the course of the primary and the secondary outcomes in the follow-up longitudinal study [61, 62].

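### Randomization is stratified by age, but the stated T2/T3 ANCOVA has no age term; if allocation is restricted within strata and age is prognostic, the reported standard errors are slightly too large

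*Protocol article*

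**What the plan says.** The protocol article, section Randomization, names one stratification factor: "Randomization will be stratified according to age". It gives no age cut-points, number of strata or blocking, and mentions only a computer-generated list.

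Section Statistical methods sets the analysis of the primary and secondary outcomes at T2/T3 as "analysis of covariance (ANCOVA) with treatment group as a fixed effect and baseline value of the respective outcome as a covariable". The Methods paragraph of the abstract gives the same covariates: "Outcomes will be analyzed with analysis of covariance, including baseline values of the respective outcomes as covariates".

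Age has one analytic role in the article, in an additional analysis: "moderating effects [60] of the following baseline variables on the primary outcome will be analyzed: ACT, gender, age, quality of life". Section Study aims likewise lists age among the moderators. Neither section puts age or the age stratum into the main treatment comparison.

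**The concern.** Stratified allocation with some restriction inside each stratum makes the arms alike on age. The difference between arms then varies less from one possible randomization to the next, because chance age imbalance no longer contributes. A model without age does not know this and leaves the age-related variation in the residual. Its standard error therefore describes a trial without that balance.

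The consequences would be confidence intervals wider and p-values larger than the design supports, and power at T3 below what the same data could give. The same two-term model serves every outcome analysed by ANCOVA, so the point reaches the secondary outcomes as well.

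**Working it through.** **1. The plan's own figure.** Section Sample size states: "sample size was calculated to detect a difference of d = 0.3 at T3 between the IG and CG". It continues: "Using alpha = 0.05 and power = 0.8, 352 participants are required". I take SD = 1, a two-sided test and 1:1 allocation. Sidedness and ratio are not stated, but these choices reproduce the figure.

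- Normal approximation: n per arm = 2(1.96 + 0.8416)² / 0.3² = 174.4, so 175 per arm and 350 in total.
- Exact noncentral t: 176 per arm, 352 in total, power 0.801. This matches.
- One-sided: 276 in total, which does not match.
- Drop-out: 352 / (1 − 0.30) = 502.9, so 503 against the stated 504. This matches within rounding.

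The sample size is sound and does not depend on the point raised here.

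**2. Size of the effect.** Let R² be the share of residual variance (given treatment group and the outcome's baseline value) that the age term explains. The article gives no value, so I assume 0 to 10%. Assume also that the strata are balanced between arms. Put f = √(1 − R²).

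- Reported SE without age relative to the true SE: 1/f.
- Actual two-sided alpha without age: 2[1 − Φ(1.96/f)].
- Power without age: Φ[(0.3/s − 1.96)/f], where s = √(2/176) = 0.1066 and 0.3/s = 2.814.
- Power with age: Φ[0.3/(s·f) − 1.96].

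Here 0.3 is in units of the residual SD of the two-term model.

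| R² (assumed) | f | SE too large by | Actual alpha | Power without age | Power with age |
|---|---|---|---|---|---|
| 0 | 1.000 | 0% | 0.050 | 0.804 | 0.804 |
| 1% | 0.995 | 0.5% | 0.049 | 0.805 | 0.807 |
| 2% | 0.990 | 1.0% | 0.048 | 0.806 | 0.811 |
| 5% | 0.975 | 2.6% | 0.044 | 0.810 | 0.823 |
| 10% | 0.949 | 5.4% | 0.039 | 0.816 | 0.843 |

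**3. Does the result depend on how patients are allocated within strata?** It does. I simulated N = 352 with two age strata, a partial correlation of 0.3 between stratum and outcome (R² = 9%), no treatment effect and 3,000 runs per setting.

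| Allocation within strata | Model | Mean reported SE | Empirical SD of estimate | Rejection rate |
|---|---|---|---|---|
| Permuted blocks of 4 | without age | 0.107 | 0.102 | 0.039 |
| Permuted blocks of 4 | with age | 0.102 | 0.102 | 0.049 |
| Simple | without age | 0.107 | 0.107 | 0.054 |
| Simple | with age | 0.102 | 0.101 | 0.054 |

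The Monte Carlo error of a rejection rate near 0.05 is √(0.05 × 0.95/3000) = 0.004.

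Under blocking, the estimate has the same spread with or without age (0.102). Only the reported SE of the two-term model is off. Under simple allocation, the SE without age is correct, and adding age reduces both the true and the reported spread.

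**The case against.** Much of the case on the other side stands.

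- **Blocking is not stated.** An overstated SE needs restricted allocation within strata. Stratification has little purpose without some restriction, so blocking is likely, but the article does not confirm it. The overstatement is conditional.
- **The prognostic value of age is unknown.** Nothing in the article says how far age predicts T3 ACT beyond baseline ACT. For an outcome that age does not predict, nothing is lost.
- **The tabulated figures are close to upper limits for each R².** They assume near-perfect age balance among the patients analysed. Section Sample size allows for 30% drop-out, and section Patient selection removes patients whose diagnosis is not confirmed at admission. Either could disturb the balance.
- **The effect is small.** In the table, power without age never falls below the planned 0.80.
- **A condensed article may leave model detail to an analysis plan.** This carries less weight here. The article names the model's covariates in two places and gives age a different role. The moderator model would normally carry an age main effect, but it is a separate analysis, planned for the primary outcome only.

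A reader might also infer that age is missing from the multiple-imputation model. The article does not list the imputation variables, which is ordinary analysis-plan detail, so that inference has no support.

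**Conclusion.** The mismatch between randomization and analysis is in the text, and adjusting for the stratification factor would improve the plan. It is a minor point about efficiency. Given restricted allocation within strata and an age effect explaining 1% to 10% of residual variance (both assumptions), the reported SE is about 0.5% to 5.4% too large and the actual alpha about 0.049 to 0.039. With no age effect the discrepancy is zero. With simple allocation there is no discrepancy in the SE, only an unused gain in precision.

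Two stronger readings are not supported. A reader might conclude that the precision gained by stratifying is lost. With balanced strata the treatment estimate keeps it, and what falls short is its reflection in the reported SE, the interval and the power. A reader might also conclude that the primary analysis is invalid. Leaving age out causes neither bias nor type I error inflation, and any error is on the conservative side.

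**What to change.** Add the age stratum used in randomization, or age as a continuous covariate, as a fixed term in the T2/T3 ANCOVAs of the primary and secondary outcomes. Record the change before outcome data are examined by arm, so that the choice of covariate cannot look data-driven. State as well whether allocation was blocked within strata, since that settles which of the two situations above applies.

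Age is already known, because it was used for allocation. The cost is one or a few degrees of freedom out of several hundred. The planned 352 evaluable and 504 recruited patients stay as they are.

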### Blinding

Patients themselves cannot be blinded due to the time-point of the start of their inpatient rehabilitation. However, those who deliver the rehabilitation treatment are unaware whether the patient is a study participant, a participant of the IG or the CG, or a regular inpatient outside the study.

### Sample size

Calculation of sample size is based on our primary outcome, the ACT, assessed three months after the inpatient rehabilitation. A previous longitudinal study of asthma patients in the Bad Reichenhall Clinic (without a CG) showed changes between start of inpatient rehabilitation and three months after inpatient rehabilitation of (Cohen’s) d > 0.5 [25]. However, this value might overestimate the effect of inpatient rehabilitation compared to a control group. Therefore, sample size was calculated to detect a difference of d = 0.3 at T3 between the IG and CG. Using alpha = 0.05 and power = 0.8, 352 participants are required, but assuming a drop-out rate of 30%, a total of n = 504 patients will be recruited [26].

Latent curve models will be used to analyze the course of the primary outcome in the longitudinal follow-up study. As a rule of thumb, N > 100 cases should be included in the computation of these models. Even with a conservatively estimated drop-out rate of 50% until T6 for IG and T8 for CG, N = 152 patients would remain in the study, which is sufficient.

### Intervention

As shown in Fig. 1, both groups receive a 3-week PR that meets the structural requirements of German healthcare insurance providers [31, 32]. The PR is carried out by a multi-professional team (physicians, psychologists, physiotherapists, sports scientists, social workers, nutritional consultants) and will be tailored individually to each patient’s needs. The rehabilitation program will be reviewed at least once a week as part of the doctor’s weekly rehabilitation ward round.

The rehabilitation program includes the following non-drug therapy components (O = obligatory for all participants, except those with individual contraindications, F = facultative if needed):Physical training (O) consisting of three obligatory components: a) endurance training scheduled for 5 units per week for 45–60 min each, during which outdoor sports and training in water (e.g. Aqua Fitness, Nordic Walking) are performed. Exercise intensity is controlled by BORG Scale and heart rate; b) strength training scheduled for 3 sessions per week of 45–60 min each and c) whole-body vibration-training scheduled 7 times per week. In addition, inspiratory muscle training (F) is provided for patients with inspiratory muscle weakness and is scheduled for 7 sessions per week, each for 21 min, of which 2 per week are supervised.Comprehensive patient education (O) consisting of two obligatory components: a.) patient education regarding asthma for one week with 7 units of 45 min; b.) one session of practical medical inhalation training and/or peak flow meter use for 60 min. In addition, patients also receive allergy awareness and trigger avoidance training (F) if required (one 60-min session).Respiratory physiotherapy (O) consisting of 3 units of group respiratory physiotherapy per week with learning of pursed lips breathing (O) for 45 min each. If necessary, patients may also receive the following optional components (F) including: a) individual breathing training by physiotherapists; b) training of Buteyko breathing techniques [29] for patients with dysfunctional breathing [30]; c) physiotherapy seminar on coughing techniques for patients with cough problems; d) mucolytic inhalation therapies (e.g. saline inhalation, for patients with mucostasis (4).Psychosocial support (F) such as social counseling, individual psychological counseling and/or group therapy will be offered if necessary (Patient Health Questionnaire (PHQ-9) > 9 points, Generalized Anxiety Questionnaire (GAD-7) > 9 points or if indicated by their physicians).Comprehensive smoking cessation program (F) will be offered to all smokers.Comprehensive nutritional counseling (F) will be offered to patients with food intolerance or allergies or over- and underweight.

In addition, patients will receive a routine check-up and if necessary, current asthma medications will be optimized according to the current guidelines. This is an obligatory part of the rehabilitation in Germany. Any changes to medications will be documented. Adverse events and complications during rehabilitation are recorded by the physicians on a standardized basis in the medical survey sheet at the end of rehabilitation.

### Outcomes and measures

The primary outcome is the mean change in AC, assessed by ACT. Secondary outcomes include mean changes in HRQoL, 6-min walk distance (6-MWD) and Sit-to-stand-test, lung function parameters, Eosinophils, dyspnea, depression, anxiety, smoking habits, illness representations, self-management skills, work ability, subjective prognosis of return to work, sick leave, medication beliefs and medication adherence. Measurement instruments for all outcomes and measurement occasions can be found in Table 1. Lung function parameters, 6-MWD, FeNO, and Eosinophils are assessed at the start and the end of the inpatient rehabilitation by staff of the PR. All other outcomes are assessed via questionnaires.

**Table 1 Tab1:** outcome measures

Outcome	measured by/Instrument	T0	T1	T2	T3A (CG)	T3	T4	T5	T6	T7 (CG)	T8 (CG)
Asthma control	Asthma control test (ACT) [29, 30]	X	X	X	X	X	X	X	X	X	X
Lung function, blood gases	FEV1, FEV1/VC, SRtot, VC, RV, PaO2, PaCO2, [50, 51]		IG	IG		CG	CG				
Exercise capacity	6MWT [53]										
Allergy	Total Ig E, specific Ig E-Screening (ImmunoCAP®)		IG	IG		CG	CG				
Asthmatic inflammation	Fractional exhaled nitric oxide (FeNO) [56], Eosinophils		IG	IG		CG	CG				
QoL	Saint George’s Respiratory Questionnaire (SGRQ) [35]	X	X	X	X	X	X	X	X	X	X
QoL	Asthma Quality of Life Questionnaire (AQLQ)] [36]	X	X	X	X	X	X	X	X	X	X
QoL	EQ-5D-5L [37, 38, 57]	X	X	X	X	X	X	X	X	X	X
QoL	Global Rating of Change Scale (GROC-scale) [39]			X	X	X	X	X	X	X	X
Symptoms	Numerical rating scale for dyspnoea, cough, sputum, pain [40]	X	X	X	X		X	X	X	X	X
Dysfunctional breathing	Nijmegen Questionnaire (NQ) [58]	X	X	X	X					X	X
Depression	Patient Health Questionnaire (PHQ) [59]	X	X	X	X		X	X	X	X	X
Anxiety	Generalized Anxiety Disorder Questionnaire (GAD 7) [60]	X	X	X	X		X	X	X	X	X
Fatigue	Brief Fatigue Inventory (BFI) [41]	X	X	X	X						
Illness Perception	Illness Perception Questionnaire (IPQ-R) German Version [45]	X	X	X	X		X	X	X	X	X
Resource Use	FIM-Lu, modification of FIMA [52]	X			X		X	X	X	X	X
Work ability	Work Ability Index (WAI) Items 1 and 4 [61]	X	X	X	X		X	X	X	X	X
SPoRTW	SPE-Scale [55]	X	X	X	X		X	X	X	X	X
Self-management	Health Education Impact Questionnaire (heiQ), Scale “Skill and technique acquisition”	X	X	X	X		X	X	X	X	X
Smoking habits	Questionnaire (developed)	X			X		X	X	X	X	X
Sport behaviour	Questionnaire (developed)	X			X		X	X	X	X	X
Medication beliefs	Brief Medication Questionnaire (BMQ) [62]	X	X	X	X				X	X	X
Adherence	Medication Adherence Report Scale (MARS) [63]	X	X	X	X				X	X	X
Sick leave	Questionnaire (developed)				IG		X	X	X	X	X

Notes: QoL: Quality of Life; SPoRT: Subjective prognosis of return to work; IG: assessment only in intervention group; CG: assessment only in control grou

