### Study aims

The primary aim of this RCT is to evaluate the effectiveness of PR for patients with asthma on short (end of rehabilitation) and intermediate-term (3 months after rehabilitation) outcomes as compared to a waiting-list control group. We hypothesize that pulmonary inpatient rehabilitation is superior regarding mean change in AC at 3 months after rehabilitation (primary outcome). Furthermore, we expect superior effectiveness of the pulmonary rehabilitation regarding health related quality of life (HRQoL), functional exercise capacity, dyspnea, anxiety, depression, subjective self-management skills, illness perceptions, sick leave, as well as subjective work ability (secondary outcomes). In addition, moderator effects of (a) gender, (b) age, (c) baseline AC, (d) baseline HRQoL and (e) baseline anxiety will be examined. Moreover, in a longitudinal follow-up study, the course of primary and secondary outcomes over one year and the annual costs before and after rehabilitation will be explored.

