## Methods

### Study design and data collection

We use a two part-study design, combining a randomized controlled trial (RCT) and a longitudinal follow-up design.

The main study is a randomized control superiority trial, comparing the intervention group (IG) with a waiting-list control group (CG). For legal reasons, any insurant of the statutory German Pension Insurance (GPI) whose application for medical rehabilitation was approved by the GPI will receive a rehabilitative intervention. Therefore, it is not possible to use an entirely untreated CG, but a waiting-list CG can be realized. After inpatient rehabilitation in the Bad Reichenhall Clinic has been approved by the GPI, patients receive a letter informing about the study and screening for their eligibility. If no response is received within 14 days, a reminder will be sent to the patients. If patients meet the inclusion criteria, they are asked to participate. After consent has been obtained, participants will be randomized to the IG or CG. In the IG, participants will start inpatient rehabilitation within 4 weeks after randomization. Data will be assessed at randomization (T0), at the beginning (T1), the end (T2), and three months after inpatient rehabilitation (T3). The CG will start inpatient rehabilitation five months (i.e. 20 weeks) after randomization. CG data will be assessed at randomization (T0), at four weeks (T1), at seven weeks (T2) and at 20 weeks (T3, beginning of inpatient rehabilitation) after randomization. The crucial reference intervals for the primary research questions are T0 to T2 and T0 to T3 for both IG and the CG. Since CG starts PR 19 to 20 weeks after T0, which is 3 months after the discharge time-point of IG, it will be possible to compare the results of IG with those of the (still) untreated CG during these initial 19 to 20 weeks. However, it may be possible that for the CG, arrival at the rehabilitation clinic (at T3) already has an effect on several outcome parameters. To estimate this “arrival effect”, an additional measurement time point (T3a) for the CG at 10 (+/-3) days before T3 has been included.

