#### Exercise Capacity

The 6-MWD will be measured using a track length of 30 m according to the European Respiratory Society/American Thoracic Society technical standards [53]. At T0 and T1 respectively, each patient performs the test twice with an interval of one hour. The best test will be included for analysis.

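### The planned T2/T3 ANCOVA cannot be run for lung function, eosinophils or 6-minute walk distance, because no stated schedule measures both arms at T2 or at T3

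*Protocol article*

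**What the plan says.** **Hypothesis.** Study aims says of the comparison with the waiting list: "we expect superior effectiveness of the pulmonary rehabilitation regarding health related quality of life (HRQoL), functional exercise capacity", followed by further secondary outcomes. The abstract also lists functional exercise capacity as a secondary outcome and says outcomes will be analysed by ANCOVA.

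**Analysis.** Statistical methods specifies, for primary and secondary outcomes at T2/T3, an ANCOVA "with treatment group as a fixed effect and baseline value of the respective outcome as a covariable". Outcomes and measures counts 6-MWD, lung function and eosinophils among the secondary outcomes.

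**Visits.** Study design and data collection defines the IG visits: "Data will be assessed at randomization (T0), at the beginning (T1), the end (T2), and three months after inpatient rehabilitation (T3"). For the control arm it says: "CG data will be assessed at randomization (T0), at four weeks (T1), at seven weeks (T2) and at 20 weeks (T3, beginning" of rehabilitation). It adds: "The crucial reference intervals for the primary research questions are T0 to T2 and T0 to T3 for both IG and the CG".

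**Measurement schedule.** Outcomes and measures says: "Lung function parameters, 6-MWD, FeNO, and Eosinophils are assessed at the start and the end of the inpatient rehabilitation by staff of the PR". In Table 1, the lung function row and the FeNO/eosinophil row are empty at T0, marked IG at T1 and T2, and marked CG at T3 and T4. The table note explains the code: "IG: assessment only in intervention group", with the corresponding meaning for CG.

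**A second schedule for 6-MWD.** Exercise Capacity says: "At T0 and T1 respectively, each patient performs the test twice with an interval of one hour".

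**The concern.** A waiting-list trial can compare the arms only while the control arm is still waiting, here from T0 to T3, and only on outcomes measured in both arms in that window. Tests done solely at the clinic, on admission and at discharge, fall in different calendar windows in the two arms. The protocol promises for these tests the same baseline-adjusted T2/T3 analysis as for the questionnaires, which both arms can complete at home.

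At stake is one secondary hypothesis, exercise capacity, and the stated analysis of two further secondary outcomes, lung function and eosinophils. Followed as written, the plan gives them no result. The likely substitute is an improvised contrast that could be read as randomized evidence for rehabilitation against waiting.

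**Working it through.** No sample-size figure bears on this point. The protocol's 352 evaluable and 504 recruited patients are derived for the ACT. The check is whether the measurement occasions of the two arms overlap where the model needs them.

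**Inputs**
- IG: T1 is the start of rehabilitation (nominally week 4) and T2 its end (week 7). From Study design and data collection and the abstract.
- CG: T3 is the start of rehabilitation (week 20). Rehabilitation lasts 3 weeks (Intervention section), so its end, T4, is at week 20 + 3 = 23.
- The ANCOVA needs the outcome in both arms at T2 (or at T3) and a baseline value in both arms. Baseline is taken as T0, in line with the reference intervals T0 to T2 and T0 to T3.

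**Occasions under each reading**

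| Outcome and source | IG | CG | Shared | Both arms at T2? | Both arms at T3? | T0 in both? |
|---|---|---|---|---|---|---|
| Lung function, eosinophils (Outcomes text and Table 1) | T1, T2 | T3, T4 | none | no, IG only | no, CG only | no |
| 6-MWD, Outcomes text alone | T1, T2 | T3, T4 | none | no, IG only | no, CG only | no |
| 6-MWD, Exercise Capacity alone | T0, T1 | T0, T1 | T0, T1 | no, neither | no, neither | yes |
| 6-MWD, both combined | T0, T1, T2 | T0, T1, T3, T4 | T0, T1 | no, IG only | no, CG only | yes |
| ACT (Table 1), for contrast | all | all | includes T0, T2, T3 | yes | yes | yes |

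In the first four rows the group effect at T2 or T3 cannot be estimated. The shared occasions that the Exercise Capacity section would add, T0 and T1, both come before rehabilitation has acted in either arm, so they cannot show its effect. The 6MWT row of Table 1 is blank in the text at hand. That may be a loss in extraction, and nothing here relies on it.

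**What could be compared instead**
- IG change T1 to T2 against CG change T3 to T4: both arms are then being treated, so this does not compare rehabilitation with waiting. The protocol does not propose it.
- IG at T2 against CG at T3: treated against still untreated, but 20 − 7 = 13 weeks apart. There is no baseline for lung function or eosinophils, and one for 6-MWD only if the T0 walks take place. The CG value is taken on arrival at the clinic, where the protocol itself warns of an arrival effect. The added visit T3a, meant to estimate that effect, has no entry for lung function or eosinophils in Table 1.
- If the combined 6-MWD schedule is real, the CG would also have untreated walks at weeks 0 and 4. These are not T2 or T3 values either, so a contrast with IG at T2 would again compare different times.

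**The case against.** **The Exercise Capacity section does give 6-MWD a baseline.** A reader might infer that 6-MWD is never measured in both arms together and has no T0 value. The document does not support that, because this section places walks at T0 and T1 in each patient. What stands is narrower: two sections conflict, and no combination of them reaches a shared T2 or T3 value.

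**Few of these outcomes carry a superiority hypothesis.** Study aims names functional exercise capacity, but not lung function, FeNO or eosinophils. FeNO is also missing from the list of secondary outcomes in Outcomes and measures, so the ANCOVA is not clearly promised for it and it is left out of this point. Nothing labels exercise capacity confirmatory; the powered hypothesis is the ACT three months after rehabilitation. All of this stands and limits the weight of the point.

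**A contrast of treated with untreated patients remains.** IG at T2 against CG at T3 keeps the randomized groups and bears on rehabilitation versus waiting, so it would be too strong to say that no relevant comparison exists. It is not the planned analysis, however, and it confounds treatment with a 13-week time difference and with arrival.

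**Multiple imputation or the analysis plan could fill the gap.** Imputation as planned addresses values missing at random. Here a whole arm is unmeasured at the time of interest by design, so the imputed arm mean would come from the imputation model's assumptions and not from data. An analysis plan cannot supply measurements that the schedule does not collect.

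**Conclusion.** The point holds in this form. For lung function and eosinophils the planned T2/T3 ANCOVA lacks both the comparator arm and the T0 covariate. For 6-MWD the document contradicts itself on timing, and under none of the three readings is there a value in both arms at T2 or at T3. The expected superiority in functional exercise capacity thus has no planned randomized comparison behind it.

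The size is limited. For these three outcomes no randomized patient can contribute to a same-time comparison between arms at T2 or T3. That affects one secondary hypothesis and the stated analysis of two other secondary outcomes. A reader might infer that the trial's main comparison is damaged. It is not: the ACT is scheduled in both arms at T0, T2 and T3, and the sample size and randomization are untouched.

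The conclusion assumes that the printed schedules are complete, and that exercise capacity rests on 6-MWD, the only exercise test in Table 1. The sit-to-stand test is also listed as a secondary outcome, but its timing is not stated. If it were done in both arms at T2 or T3, it would need separate consideration.

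**What to change.** 1. Reconcile Outcomes and measures with Exercise Capacity on when 6-MWD is measured in each arm, and make Table 1 agree if its 6MWT row is truly blank. Only the sponsor knows which schedule is in use. State the timing of the sit-to-stand test at the same time.
2. In Statistical methods, exclude 6-MWD, lung function and eosinophils from the T2/T3 ANCOVA.
3. In Study aims, remove functional exercise capacity from the outcomes on which superiority over the waiting list is expected, and from the matching list in the abstract.
4. Report these outcomes as within-patient changes from start to end of rehabilitation in the longitudinal part, described as uncontrolled.
5. If IG at T2 (week 7) is compared with CG at T3 (week 20), label the contrast exploratory and say that the measurements are not contemporaneous and that the CG value is open to the arrival effect.

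The cost is wording only, with no new measurements. The downside is giving up a between-group claim on a secondary outcome that the stated schedule cannot support.
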